### Inclusion and exclusion criteria

The study population consists of men from the cities of Freiburg and Mannheim with new paternity within one year prior to this survey (group 1: fathers of an infant) as well as men from the same regions without a newborn child within one year prior to this survey (group 2: control group). The two groups will be matched by age, nationality and marital status. To ensure a high external validity of our results, no exclusion criteria have been established, with the exception of insufficient German language proficiency due to the nature of the survey.

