### Recruitment

Contact details of potential study participants for both groups will be obtained from the residents’ registration offices of the chosen study regions of Freiburg and Mannheim, which will enable a random sample of fathers of an infant to be drawn. Due to the random selection of fathers of an infant, a balanced distribution of the children’s age between 0 and 12 months can be expected. Since a request for a sample from the residents’ registration offices takes two days to process, it is guaranteed that all included fathers of an infant will have become a father of a newborn within 12 months prior to this survey. At the same time, the residents’ registration offices of Freiburg and Mannheim will draw the matched control group. The information provided by the residents’ registration offices will include contact details as well as descriptions of the men in the samples according to the variables age, nationality and marital status. After obtaining these sample descriptions, information about the study and a consent form as well as a questionnaire will be sent by post to both groups. The questionnaire is reduced to central variables and a prepaid return envelope will be attached, as these measures are associated with an increased response rate [46].

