#### Prevalence

The prevalence in different time periods after childbirth will be measured as a secondary objective, assessed using the PHQ-9. The age of the child in weeks will be recorded by calculating the time between the date of childbirth and the date on which the questionnaire is completed.

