### Trial status

Enrolment for the trial began in September 2018. Recruitment and data collection continued until March 2019. As of August 2019, data management and data analysis is ongoing.

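### A two-day register request does not guarantee that responding fathers are within the first year after birth, because child age and PHQ-9 are taken later, at questionnaire completion

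*Protocol article*

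**What the plan says.** The Recruitment section gives the processing time, a request to the "registration offices takes two days to process", and from it concludes that "it is guaranteed that all included fathers of an infant will have become a father of a newborn within 12 months" prior to the survey. It also says that, because fathers are drawn at random, a balanced spread of the child's "age between 0 and 12 months can be expected".

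The same section then puts the mailing after the draw: "After obtaining these sample descriptions, information about the study and a consent form as well as a questionnaire will be sent by post to both" (that is, fathers and controls). A prepaid envelope is enclosed for the reply.

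Under Secondary objectives, Prevalence, the child's age in weeks is obtained by "calculating the time between the date of childbirth and the date on which the questionnaire is completed". Table 1 lists both dates. The Primary objective section sets the target as prevalence within the first year after childbirth.

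Inclusion and exclusion criteria define group 1 by paternity in the year before the survey and add that "no exclusion criteria have been established, with the exception of insufficient German language proficiency". The article states no birth-date margin in the draw, no return deadline, and no rule for a child who is past 12 months when the form is filled in.

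**The concern.** The guarantee rests on one short step in a longer chain. After the request come preparation of the mailing, posting, completion by the father, and return. Eligibility is fixed at the first link. Depressive symptoms and child age are measured near the last. A father whose child was close to 12 months at the draw can therefore answer after the first birthday, and no father can answer when his child is younger than his own lag.

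Two uses of the data depend on this. The primary prevalence is meant to describe the first year. The time-period analysis is said, in Sample size calculation, to be adequately powered for each month after birth. The first month is the one that loses respondents, and a thirteenth month appears. The Background itself reports that prevalence differs by time since birth, so a shifted window could move the overall rate. The article does not allow the direction to be determined.

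**Working it through.** **Inputs from the article.** 4600 fathers contacted and about 75% non-response (Sample size calculation); child ages expected to be balanced over 0 to 12 months (Recruitment); 8.0% versus 5.0%, significance level 0.05, power 80%, total 2300 (Sample size calculation).

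**Input assumed.** The lag L from draw to completion. The only time the article gives is the two days for the request, so a range is shown.

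**The plan's own figure.** Expected respondents: 9200 × 0.25 = 2300 in total and 4600 × 0.25 = 1150 fathers. For 8.0% versus 5.0%, two-sided 0.05, power 80%, the usual two-proportion formula gives 1059 per group (2118 in total), or 1125 per group (2250 in total) with continuity correction. The latter is within 3% of 2300. The stated sample size does not depend on the present point.

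**Window shift.** With age uniform on 0 to 365 days at the draw and a constant lag L, age at completion is uniform on L to 365 + L.

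- Share over 12 months = L/365; number = 1150 × L/365.
- Share of the first month (30.4 days) still observable = (30.4 − L)/30.4, and zero once L exceeds 30.4.

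| Assumed L | Over 12 months | Of 1150 fathers | First month observable |
|---|---|---|---|
| 2 days | 0.5% | 6 | 93% |
| 7 days | 1.9% | 22 | 77% |
| 14 days | 3.8% | 44 | 54% |
| 28 days | 7.7% | 88 | 8% |
| 56 days | 15.3% | 176 | 0% |

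**Unequal lags.** If lags are spread evenly over 7 to 42 days (mean 24.5), the share over 12 months is 24.5/365 = 6.7%, about 77 fathers. The share with a child under 28 days is (21²/2)/(365 × 35) = 1.7%, about 20 fathers, against 1150 × 28/365 = 88 under the balanced expectation. For comparison, an average month would hold 1150/12 ≈ 96.

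**Effect on the primary comparison.** Power = Φ[(d − 1.96·SE₀)/SE₁], where SE₀ uses the pooled proportion and SE₁ the separate ones. With 1150 per group, 8.0% versus 5.0%: SE₀ = 0.01028, SE₁ = 0.01026, so (0.03 − 0.02015)/0.01026 = 0.96 and power is 0.831. Suppose, as a further assumption, that fathers past 12 months have the control rate of 5.0% and stay in. The fathers' rate becomes 8.0% − 3.0% × L/365, and power falls to 0.805 at 14 days, 0.776 at 28 days and 0.710 at 56 days. If they are instead removed, the same formula with 1106, 1062 and 974 fathers against 1150 controls gives 0.825, 0.817 and 0.801.

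**The case against.** **The lag is not stated.** This stands. A reader might infer that the first weeks after birth are missing. The article does not support that. What follows is a gap as long as the shortest lag and thinning up to the longest, which may be days or weeks.

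**Fieldwork dates.** A reader might take "Recruitment and data collection continued until March 2019", after a start in September 2018, as evidence of long lags. It is not. Those dates bound the whole field period and say nothing about any one man's interval from draw to reply, nor whether there was one draw or several. Several draws would not remove the shift either, since each carries its own lag.

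**The sentence is about eligibility.** Group 1 is defined as men "with new paternity within one year prior to this survey (group 1: fathers of an infant"). If the survey means the mailing date, the sentence is nearly true. That reading is fair, but it does not bring measurement inside the first-year target.

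**Balance.** A uniform distribution shifted by a constant lag is still uniform. Only the endpoints move, and unequal lags blur the ends. The expectation of balance is therefore not refuted; it describes the draw rather than completion.

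**Handling may be settled elsewhere.** The article does not say that fathers past 12 months are kept in the primary set, and the absence of further exclusions does not cancel the inclusion criterion. Age at completion is already recorded and already defines the time periods. All this is true, and a missing analysis-set rule alone would be no finding. What remains is an affirmative guarantee that the described procedure does not deliver, and that hides the need for such a rule.

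**Conclusion.** The guarantee does not follow from its premise. Eligibility is fixed at the draw, while child age and PHQ-9 are taken at completion. Any positive lag therefore puts some responding fathers beyond 12 months and removes or thins the earliest days after birth.

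The size rests on three assumptions: the lag, ages evenly spread at the draw, and response unrelated to child age. For lags of 1 to 8 weeks, roughly 2% to 15% of responding fathers would be past 12 months. At a few days the number is negligible.

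No bias in the primary contrast is shown, and with short lags the effect on it is small. The power losses above need the added assumption that fathers return to the control rate as soon as the child passes 12 months. The first month of the time-period analysis is more exposed, and those observations cannot be recovered. This is a correctable defect of definition and wording, not one that undermines the comparison.

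**What to change.** 1. Replace the guarantee with a statement that eligibility is set at the register draw and that child age is determined at completion.
2. Restrict the primary first-year analysis to fathers whose child is at most 12 months old at completion, using the birth and completion dates already collected. Report all responding fathers as a sensitivity analysis.
3. Report the achieved distribution of child age at completion and the age range actually covered, with the count in the first month shown separately, so that first-year and by-month statements are limited to what was observed.

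No new data are needed, and Trial status describes data management and analysis as ongoing. The cost is about L/365 of father respondents. At 4 weeks that is 88 of 1150, and power for 8.0% versus 5.0% goes from 0.831 to about 0.817. With shorter lags the loss is smaller. The unobserved earliest days cannot be restored by analysis, only declared.

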### Primary objective

The primary objective is to assess the prevalence of PPD in fathers within the first year after childbirth (group 1: fathers of an infant) compared to the prevalence of depressive symptoms in a matched sample without recent paternity (group 2: control group). This will enable the relative frequency of depressive symptoms after childbirth to be calculated. For prevalence estimates regarding PPD in fathers of an infant and regarding depressive symptoms in the control group, respectively, the Patient Health Questionnaire (PHQ-9) will be used as a measurement instrument in both groups. With sensitivity and specificity both lying at 88% [41], the PHQ-9 shows good psychometric properties and is therefore recommended by the DSM-5 for measuring symptom severity [47]. A particular advantage of the PHQ-9 is that it can be evaluated categorically, taking into account the presence of major and additional symptoms in the diagnosis. Moreover, standard data from other studies are available for the PHQ-9 [48]. Table 1 shows the measurements to be applied to examine primary and secondary objectives in both groups (cf. Table 1).

### Secondary objectives

Secondary objectives will be addressed regarding the prevalence of PPD in different periods after childbirth, male-specific symptomatology, and risk factors of PPD. On a healthcare level, service utilization regarding PPD in fathers is considered as a secondary objective.

#### Prevalence

The prevalence in different time periods after childbirth will be measured as a secondary objective, assessed using the PHQ-9. The age of the child in weeks will be recorded by calculating the time between the date of childbirth and the date on which the questionnaire is completed.

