## Background

While postpartum depression in mothers is a well-researched and recognized mental illness [1], growing evidence suggests that fathers in the postpartum period are also at increased risk of developing depressive symptoms [2–6]. Studies have indicated that the prevalence of depressive symptoms during pregnancy and the postpartum period in fathers is similar to that of mothers [4, 5, 7, 8]. A recent meta-analysis by Cameron et al. (2016) revealed a total rate of depression of 8.4% in fathers during pregnancy and up to one year postpartum, with a higher prevalence of 13% in the 3- to 6-month postpartum period [9]. An earlier meta-analysis by Paulson and Bazemore (2010) yielded a prevalence of 10.4% for depression in fathers during the postpartum period [10]. The authors found that prevalence estimates were moderated by the time of measurement, with higher depression rates of 25.6% during the 3- to 6-month postpartum period [10]. However, due to factors such as study location and methods, prevalence rates vary broadly, ranging from 4 to 25% [4, 10–13]. The varying rates of paternal postpartum depression (PPD) in different countries might be influenced by cultural biases, e.g., differing interpretations of depressive symptoms, social acceptance of mental health problems or divergent expectations with respect to paternal infant care responsibilities. Additionally, methodological aspects such as the use of different diagnostic approaches, biased translations of instruments, or differing sampling methods may also impact PPD prevalence data.

For Germany, there is currently only one longitudinal study by Gawlik et al. (2014), which examined paternal depressive symptoms over the second and third trimester of pregnancy up to 6 weeks postpartum using the Edinburgh Postnatal Depression Scale [14, 15]. The study found that 7.8% of fathers showed depressive symptoms in the postpartum period. Although these findings suggest a scientific and public importance of PPD for Germany, the study only provided information about PPD up to 6 weeks after birth, thus omitting the majority of the postpartum period. Furthermore, the available research is unable to answer the question of whether depressive symptoms are more common in fathers in the postpartum period than in men without a newborn child.

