#### Sample size calculation

The study will investigate whether a significant difference can be observed between the prevalence of PPD in fathers within the first year after childbirth and the prevalence of depressive symptoms in a matched sample of men without recent paternity. The a priori calculation of statistical power is based on a point prevalence of 5.3% in the control group (95% confidence interval 4.3–6.3%), which corresponds to the incidence of depressive symptoms in men according to the PHQ-9 standard data [48]. Compared to reported prevalence rates, an increase of more than 50% in the point prevalence in fathers of an infant would be relevant. This corresponds to a point prevalence of at least 8.0%. According to the meta-analysis by Cameron et al. (2016), the point prevalence of PPD in fathers in the first year after childbirth lies between 7.2 and 9.6% [9]. Therefore, a potential prevalence of 8.0% is not only a realistic outcome considering the results of previous studies, but would also represent a relevant increase in the rate of depressive symptoms. To be able to detect the difference between the population prevalence of 8.0% in fathers of an infant and 5.0% in the control group with a significance level of 0.05 and a power of 80% in a Chi-square test, data from a total sample size of 2300 participants are necessary.

In Freiburg and Mannheim together, about 5500 children are born each year [61, 62]. Out of these, 4600 fathers of an infant will be randomly selected, meaning 2300 fathers of an infant per city. In addition, a control group (*n* = 4600; 2300 per city) matched according to age, nationality, and marital status will be generated. Thus, a total of 9200 potential participants will be contacted. Based on response rates from other anonymized postal surveys, a dropout rate of about 75% is expected for this study. Already included in these dropout calculations are those men who cannot participate due to incorrect address information. However, the obtained sample size will be sufficiently large to reveal small differences in the prevalence of depressive symptoms among the fathers of an infant (ω = 0.1) for each month after birth with a power > 80% using the Chi-square test.

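### The only test tied to the time course after birth is a chi-square test by month, which has less power for a 3- to 6-month peak of 13% than low-df tests on the same data

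*Protocol article*

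**What the plan says.** Under Secondary objectives, Prevalence, the protocol article states "The prevalence in different time periods after childbirth will be measured as a secondary objective, assessed using the PHQ-9", and adds "The age of the child in weeks will be recorded". That section speaks of periods in general. It fixes neither cut-points nor a test.

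A unit and a test appear together only at the end of Sample size calculation. There the sample is called large enough to show small differences between fathers, at ω = 0.1, "for each month after birth with a power" above 80%; the test named is chi-square. The Analyses section is in line with this: nominal distributions are compared by chi-square or Fisher's exact test. It also lists logistic regression for socio-demographic and other influencing factors, without naming child age.

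The Background gives an expectation about the shape. The more recent meta-analysis reports 8.4% overall, "with a higher prevalence of 13% in the 3- to 6-month postpartum period". The earlier one reports 10.4% overall and 25.6% at 3 to 6 months.

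**The concern.** A chi-square test over twelve months treats them as interchangeable labels. It spends 11 degrees of freedom, ignores the order of time, and discards the age in weeks that the survey collects. It also makes no use of the one feature of the time course that the Background reports from both meta-analyses, a higher rate at 3 to 6 months.

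Each month would hold about 96 fathers and 8 cases, so single monthly rates are imprecise. At stake is a secondary objective. A real peak of moderate size could go undetected, or attention could fall on one noisy month chosen after the fact.

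**Working it through.** **Inputs**
- Fathers contacted: 4600 (Sample size calculation: "Out of these, 4600 fathers of an infant will be randomly selected, meaning 2300 fathers of an infant per city").
- Response: 25%, because "a dropout rate of about 75% is expected for this study". Responding fathers: 4600 × 0.25 = 1150.
- Child age: evenly spread over 0-12 months (Recruitment), so 1150/12 ≈ 96 fathers per month.
- Alpha: 0.05. The article states it for the primary test ("with a significance level of 0.05 and a power of 80% in a Chi-square test"); it is assumed here for the time course.
- Peak rates: from the Background, as above.

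**The plan's own power figure.** Power comes from the noncentral chi-square distribution with noncentrality λ = n·ω². With n = 1150 and ω = 0.1, λ = 11.5.

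| df | Power at ω = 0.1, n = 1150 |
|---|---|
| 11 (twelve months) | 60% |
| 3 | 82% |
| 2 | 87% |
| 1 | 92% |

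The stated figure of more than 80% is therefore not reproduced for a twelve-month comparison; that would need 1681 fathers. Of the df tried, it is reached at 3 df or fewer. Counting all 2300 respondents gives 93% at 11 df, but half of these are controls, who have no infant's age to analyse.

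**A 13% peak at 3-6 months, year average 8.4%**
- Rate in the other nine months: (0.084 − 0.25 × 0.13)/0.75 = 0.0687.
- ω² = [0.25 × (0.13 − 0.084)² + 0.75 × (0.0687 − 0.084)²] / (0.084 × 0.916) = 0.00917, so ω ≈ 0.096.
- λ = 1150 × 0.00917 ≈ 10.5.

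**Power under this and other readings of the 13% peak**

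| Fathers; assumption | 12 months, 11 df | 4 quarters, 3 df | 3-6 months vs rest, 1 df |
|---|---|---|---|
| 1150; year average 8.4% | 55% | 79% | 90% |
| 1150; year average 8.0% | 67% | 87% | 95% |
| 1150; 8.0% in the other months | 33% | 55% | 72% |
| 1150; 8.4% in the other months | 27% | 46% | 63% |
| 920; year average 8.4% | 44% | 68% | 83% |

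Simulation of the first row (20,000 surveys) gives 52%, 75% and 87%, close to the formula. For 80% power in that row the monthly test would need about 1835 fathers.

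**The larger cited peak.** For 25.6% against a year average of 10.4%, ω ≈ 0.29 and power is practically 100% for every test in the table.

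**Shape of the course.** The table assumes a sharp step that coincides with the second quarter. For a smooth hump, simulation gives 51% (12 months), 77% (3-df spline in weeks) and 80% (contrast). For the sharp step of the first row, a spline smooths over the edges and gains little: 4,000 simulated surveys, with knots at the 5th, 35th, 65th and 95th percentiles of age in weeks, give 56%. The contrast carries the gain for a step; the spline gains for a smooth course.

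**Precision of one month.** 1.96 × √(0.084 × 0.916/96) ≈ 0.055, or ±5.5 points. The difference between 13% and 8.4% is 4.6 points.

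**The case against.** The strongest reply is that the article never lays down the monthly chi-square as an analysis rule. The Prevalence section names no test, the Study design and Discussion sections speak of several periods, and months appear only in a remark on power. An article may leave cut-points and model terms to a fuller document, and the logistic regression under Analyses could take child age as a factor. This stands in part. A reader might infer that the protocol prescribes a test of unordered months; the text supports only that this is the sole unit and test attached to the objective. That is still a stated choice, not a detail left open.

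Further points stand:
- The chi-square family is not at fault. Four quarters would do well; the number of unordered categories is what costs power.
- The only formal hypothesis under Objectives concerns fathers versus controls, and the Background warns that rates vary widely with place and method. Making a 3-6 month contrast the sole test would be partly a preference.
- Trial status says that data collection ended in March 2019 and that analysis was under way in August 2019, so a contrast added now is not automatically prespecified.

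None of this removes the loss of power. In every row of the table the tests with fewer degrees of freedom gain 19 to 39 points.

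**Conclusion.** The point holds in a limited form. For a 13% rate at 3-6 months, the one test the article attaches to this objective has about 55% power, against about 79% for quarters and 87-90% for a single contrast. This rests on 1150 responding fathers, equal months, alpha 0.05 and 8.4% as the first-year average. The last is an assumption, because the cited 8.4% also covers pregnancy. Over the readings at 1150 fathers the monthly test runs from about 27% to 67%, so it misses the peak about 33% to 73% of the time.

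Two stronger conclusions are tempting and not supported. A reader might infer that the objective will probably end in a null result, but at 55% power detection is slightly more likely than not. A reader might also infer that either cited peak would often be missed, but the 25.6% peak would be found by any of these tests. The matter concerns a secondary objective and leaves the primary comparison untouched.

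**What to change.** In Analyses and in the last sentence of Sample size calculation:

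1. Replace the month-by-month chi-square as the test of this objective with logistic regression of PHQ-9 case status on child age in weeks, using a restricted cubic spline (3 df), shown with its 95% band.
2. Add one contrast of 3-6 months with the remaining months. Fix it in writing before the time-course data are examined, and label it as motivated by the cited meta-analyses. If the data have already been examined, label it exploratory.
3. Keep monthly prevalences with confidence intervals as description only.
4. Restate the power sentence for the tests actually used.

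The cost is wording only, since the birth date, completion date and PHQ-9 are all collected. The downside is that the contrast loses power if the peak lies elsewhere, which the spline covers, while the spline gains little for an abrupt step, which the contrast covers. The two should therefore be reported together, with the spline named in advance as the test of the objective, so that the smaller p-value is not picked afterwards.
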